From the available literature, the largest dose of *R.rosea* taken for the longest period of time without side effects is 340 mg twice per day over a six week period. No other adverse effects from case studies or case reports have been identified and available clinical evidence suggests *R. rosea* has a safe profile with little toxicity. The lethal dose of *R. rosea*, at which 50% of animals die (LD50), has previously been found to be 3360mg/kg in rats (35). Equivalence calculations have indicated that in adult humans, LD50 would be approximately 235,000 mg/kg(36). Clinical studies in the literature report *R. rosea*-only products ranging in dose from 50 mg to 660mg *R. rosea* extract per capsule, to a maximum of 1500mg/day suggesting a large margin of safety. Further, *R. rosea* is available in Canada as a natural health product (i.e. for over-the-counter use as self-care, without a physician’s supervision). In the United States, it is marketed as a dietary supplement which are deemed safe based on a documented history of use or other evidence of safety unless proven otherwise (37). While neither Health Canada nor its US counter-part has issued any safety concerns about *R. rosea,* one product containing *R. rosea* was recalled by the Food and Drug Administration in December 2008 for adulteration with a drug product (hydroxyhomosildenafil – an analog of the active ingredient in a drug used for erectile dysfunction).

Although no contraindications with other herbal or prescription medications currently exist, we postulate that *R. rosea* may have an additive effect with other substances exhibiting stimulant properties and such combination is contraindicated (38). Like many natural health products, the likelihood of adequate reporting of adverse events may be lower than conventional medications due to the inconsistent nature in which patients encounter NHPs – non-standard doses, varying durations and combined with any number of other NHPs or conventional medicines (39).

No safety information currently exists for pediatric, breast-feeding and pregnant populations.

- - 1. RHODIOLA ROSEA FORMULATION TO BE USED

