**The following interventions will be supplied:**

1. ***Rhodiola rosea* extract standardized to2.8% rosavins (**29.0 % microcrystalline cellulose, 0.5% Silicon dioxide
2. **Placebo (**95% microcrystalline cellulose, 0.5% Silicon dioxide)

**Both interventions will be encapsulated in gelatine capsules, which are an animal-based product, and will look identical. Medications will be packaged in identical bottles labelled according to the participants’ randomization code.**

Development of the both interventions will be undertaken by [name] [name], a pharmacist and assistant professor in the Faculty of Pharmacy and Pharmaceutical Sciences at the University of Alberta. [name], will store all trial medications (*R. rosea* and placebo) in a secured storage facility until recruitment. Study medication will then be given to the study nurse for dispensing at time of enrolment; medication will be stored under lock and key accessible only by the study nurse until time of dispensing.

- 1. Treatment regimen

The trial will begin on the day that subjects start their clinical rotations and end 6 weeks later. Subjects will be instructed to take two to four capsules of the trial medication per 24 hour period (see section 6.2). All outcomes will be measured at baseline (Day 0) and at the end of the trial period (week 6). The project coordinator will phone participants on the day(s) leading up to their baseline assessment to remind them to complete their questionnaires and ensure they are comfortable with the study procedures. The primary outcome and two secondary outcomes will be measured again at the end of each week; all other outcomes will be measured daily (see section 7). Subjects will be prompted to report adverse events daily during the trial period and at the end of their clinical rotation four weeks after completion of the trial. During the trial period, the study nurse will phone participants in week 2 and week 5to remind them to complete their questionnaires and to inquire about adverse events (see section 7.1.2).

- 1. DOSE AND DURATION

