**Each *R.rosea* capsule will contain 182.0 mg of the product.** Participants will be asked to take two capsules of the trial medication at the start of their wakeful period each day. Since fatigue is a subjective symptom, participants will be asked to self-determine their need for a second dose of the trial medication within the four hour period after the initial dose. The second dose willbe one capsule~~;~~ the daily MYMOP will ask participants to record the number of capsules ingested in the past 24 hours.

***Dose & duration justification:*** Since the majority of previous trials that found significant effects assess long-term, rather than acute supplementation of *R. rosea*, this trial will examine efficacy over a similar duration yet with an aim to overcome limitations of previous studies. **Based on dose and duration information previous studies of** R. rosea **for mental and physical performance (Table 2), the maximum dose of** R. rosea **without adverse effects is 1500 mg over three days (short-term supplementation). The maximum dose that has been safely used in long-term supplementation is 680 mg standardized to 3.0% rosavins for a six week period. The *R.rosea* formulation being used in this trial has been standardized to contain 2.8% rosavins; therefore the equivalent maximum daily dose for this study is 546 mg.**

- 1. **Treatment allocation**

**Partcipants will be assigned to a treatment group (either *R.rosea* or placebo) according to a computer generated randomisation scheme produced by our data management team at the Epidemiology Coordinating and Research Centre at the University of Alberta.** Sampling will be stratified by night vs. rotational shift workers and a permuted block randomization technique will be used with permuted block sizes of 4. Although the nursing profession is dominated by females, there has been no consistent association between fatigue and gender and therefore randomization will not be stratified by gender.

**The Investigator will be supplied with individual code-break envelopes for each patient, containing details of the patient’s treatment. Sealed copies of the randomisation code will also be retained by the study pharmacist, [name]** [name]**.**

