| Karpova 1999(60) | Single-arm cohort study | | 10 | | Elderly males; 60-74 y | | 45 mL of 40-plant mixture containing RR (no proportion, concentration of constituents) | | Daily dose for 1 month | | Non-specific haematological parameters including number of leukocytes, erythrocytes haemoglobin | | Significant improvement in 6/9 parameters | |
| Bocharova 1995(61) | Single-arm cohort study | | 12 | | Bladder cancer | | 3 mL liquid extract of RR | | Twice daily for 2 months followed by a 2 week wash-out period; this cycle for a total of 18 months | | frequency of relapse, tissue disintegration, immune status | | No significant effect | |

Table 2

Dose and duration of *R. rosea* treatment in physical and mental health studies; *n.s.: not stated; wo: washout*

| STUDY | DOSE (RR extract) | % rosavins | FREQUENCY | DAILY DOSE RR | DURATION (Days) |
| --- | --- | --- | --- | --- | --- |
| Darbinyan 2000 | 170 mg | n.s. | Once/day | 170 mg | 14  14 d wo |
| Shevstov 2003 | 2x185mg  3x185mg | n.s. | single dose  single dose | 370 mg  555 mg | 1 |
| Spasov 2000a | 2x50 mg | n.s. | Not stated | 100 mg | 20 |
| Spasov 2000b | 660mg | n.s. | Not stated | 660 mg | 20 |
| Abidov 2004 | 340 mg | n.s. | Twice/day | 680 mg | 36 |
| Colson 2005 | 2x300 mg  1x300 mg  (herbal supplement) | 3.0% | Once/day  Once/day | 600 mg  300 mg | 6  7 |
| De Bock 2004a | 2x100 | 3.0% | Once/day | 200 mg | 2 |
| De Bock 2004b | 100 | 3.0% | Twice/day | 200 mg | 28 |
| Earnest 2004 | 2x300 mg  1x300 mg  (herbal supplement) | 3.0% | Once/day  Once/day | 600 mg  300 mg | 4  11 |
| Walker 2007 | 2x250 mg  4x250 mg | 3.0% | Thrice/day  Single dose | 1500 mg  1000 mg | 3  1  7 d wo |
| Fintelmann 2007 | 2 capsules  2 capsules  (No dose given) | n.s. | Once/day  Twice/day | N/A | 84 |
| Darbinyan 2007 | 2x170 mg  2x170 mg | 3.0% | Once  Twice/day | 340 mg  680 mg | 42 |
| Bystritsky 2008 | 1x170 mg | n.s. | Twice daily | 340 mg | 70 |

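### Section 6.1 allows up to four capsules a day and section 6.2 at most three, and the 546 mg that 6.2 calls equivalent to the reference dose is only 75% of it

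*Protocol*

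**What the plan says.** Section 6.1 (Treatment regimen) gives the daily range: "Subjects will be instructed to take two to four capsules of the trial medication per 24 hour period (see section 6.2". Section 6.2 (Dose and duration) has participants take two capsules on waking and decide for themselves, within the next four hours, whether they need a further dose. On its size it says "The second dose willbe one capsule". On strength, each active "capsule will contain 182.0 mg of the product".

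Section 6.2 then justifies the ceiling. The reference is stated as "The maximum dose that has been safely used in long-term supplementation is 680 mg standardized to 3.0% rosavins for a six week period". The trial product is standardised to 2.8% rosavins, and the section concludes "therefore the equivalent maximum daily dose for this study is 546 mg".

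Three other places bear on this:
- Section 1.2.3 gives the same reference regimen as the largest dose "taken for the longest period of time without side effects is 340 mg twice per day over a six week period".
- Table 2 lists the 42-day trial in mild to moderate depression at 3.0% rosavins, with two 170 mg units taken once or twice a day (340 or 680 mg).
- Section 6.6 says participants will be told that the trial dose is the highest with evidence of safety behind it.

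**The concern.** Two things look wrong. First, the upper limit is four capsules in one section and three in the next, although the first section cites the second as its source. Second, the conversion runs the wrong way. A product with fewer rosavins per milligram needs more milligrams to match the reference, yet the stated equivalent falls from 680 to 546 mg.

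The optional dose is left to the participant, so the ceiling is the working instruction. The study nurse hands over a six-week supply at enrolment and would have two different maxima to explain and two different counts to dispense. A four-capsule day complies with 6.1 and breaches 6.2. If three capsules is the true regimen, the trial tests about three quarters of the reference dose while describing it as equivalent, and a reader of a null result would be misled about how much was tested.

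**Working it through.** **Inputs.** From 6.1: 2 to 4 capsules a day. From 6.2: 2 capsules plus 1 optional; 182 mg per capsule; reference 680 mg a day at 3.0% rosavins; trial product 2.8%; stated maximum 546 mg. From Table 2: reference unit 170 mg. From section 6: excipients "29.0 % microcrystalline cellulose, 0.5% Silicon dioxide".

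**1. Where 546 mg comes from.** Capsules × 182 mg:
- 2 × 182 = 364 mg
- 3 × 182 = 546 mg
- 4 × 182 = 728 mg

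The stated maximum is exactly three capsules, which confirms that 6.2 means two plus one. The upper end of 6.1 is 728/546 = 1.33 times that maximum.

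**2. The conversion that 6.2 describes.**
- Rosavins in the reference: 680 × 0.030 = 20.4 mg.
- Equivalent at 2.8%: 680 × 3.0/2.8 = 728.6 mg, and 728.6/182 = 4.00 capsules.
- Stated figure against this: 546/728.6 = 0.749.

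Other routes do not give 546 either. The inverted ratio gives 680 × 2.8/3.0 = 634.7 mg, and no conversion gives 680 mg. For 546 mg to carry 20.4 mg, the product would need 20.4/546 = 3.74% rosavins.

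**3. Rosavins delivered, with 2.8% applied to the whole 182 mg.**
- Three capsules: 546 × 0.028 = 15.3 mg, or 75% of 20.4 mg.
- Four capsules: 728 × 0.028 = 20.4 mg, or 99.9%.

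**4. The capsule strength.** Converting the 170 mg reference unit gives 170 × 3.0/2.8 = 182.1 mg. One trial capsule therefore matches one reference unit, and the 680 mg reference is four such units. The capsule size fits a four-capsule day.

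**5. Sensitivity (assumption).** Suppose 182 mg includes the 29.0% + 0.5% = 29.5% excipients and 2.8% applies only to the remaining 70.5%:
- Three capsules: 546 × 0.705 × 0.028 = 10.8 mg (53%).
- Four capsules: 728 × 0.705 × 0.028 = 14.4 mg (70%).

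Under either reading 546 mg is not the equivalent, and four capsules do not exceed the reference in rosavins.

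**6. Supply for 42 days.** 42 × 3 = 126 capsules, or 42 × 4 = 168.

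**The case against.** The strongest reply is that 6.2 plainly governs. Section 6.1 is a summary that defers to it, 6.2 is the dedicated dose section, and it agrees with itself on the maximum (2 + 1 capsules, 546 mg). On that view the repair is one word in 6.1 plus a corrected justification, and the match between 182 mg and the converted 170 mg shows only how the capsule was sized. It may also be said that nobody is put at risk, that the daily questionnaire records the number of capsules taken, and that section 8.2 plans to examine dose as a covariate. Finally, 6.2 attributes the 2.8% to the formulation, which leaves little room for the extract-only reading, and the protocol states no capsule count for the supply.

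Much of this stands. Section 6.2 is the likelier text to govern, the harm is limited, the extract-only figures are a side check, and the supply counts are a consequence rather than a stated error. But even with 6.2 governing, three statements stay wrong: the range in 6.1, the claim of equivalence in 6.2, and the description of the dose in 6.6. The arithmetic in 6.2 and the capsule size both point to four, so the text alone does not settle which number was intended. Recording actual intake does not tell participants or the nurse what the limit is.

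**Conclusion.** The concern holds, and it should be fixed before dispensing. The daily maximum is stated as 728 mg in effect (6.1) and as 546 mg (6.2), a difference of one third. The 546 mg is not the rosavin equivalent of 680 mg at 3.0%. The correct figure is 728.6 mg, and 546 mg is about 75% of it, or 53% on the extract-only assumption. The wording in 6.6 does not fit a 546 mg ceiling, since 1.2.3 and 6.2 both report 680 mg a day for six weeks as safely used.

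This rests on rosavin content as the measure of equivalence, which is the basis 6.2 itself uses. On that basis the error is conservative, because neither section leads to more rosavins than the reference. The randomised comparison, sample size and primary analysis are untouched. What suffers is the clarity of the instruction and the description of the dose tested.

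**What to change.** The clinical team should choose the maximum, and the text should then follow one of two routes.

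- **Three capsules.** In 6.1, change the range to two to three capsules. In 6.2, present 546 mg as the chosen trial maximum, about 75% of the 728.6 mg rosavin equivalent, and drop the claim that it follows from the conversion. In 6.6, say the dose lies within what safety evidence supports, not that it is the highest.
- **Four capsules.** In 6.2, make the second dose up to two capsules and the maximum 728 mg.

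In either case, confirm in 6.2 that 2.8% refers to the whole 182 mg and set the six-week supply to match (126 or 168 capsules). The cost is a few sentences in 6.1, 6.2 and, for three capsules, 6.6, plus a capsule count. Design, sample size and analysis do not change.

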**The code for a patient will only be opened in an emergency, when it is necessary for a patient’s treatment to be disclosed. If a code is broken the investigator will inform the Study Director/Monitor and document the details of the reason in the patient’s case report forms.**

- 1. ALLOCATION CONCEALMENT

Participants will receive a sealed, serially-numbered opaque bottle containing the study medication or placebo depending on their randomised group assignment. They will be provided a six-week supply of their assigned study medication.

- 1. BLINDING

**The placebo capsule will have the same appearance, volume, weight, odour and taste as the *R.rosea* product so that neither the participant nor trial personnel know who is receiving which medication. The effectiveness of the blind will be assessed at the beginning of the study after a single dose via the MYMOP on Day 1. Participants will be asked to guess which medication they think they were allocated to.**

- 1. **CO-INTERVENTION AND CONTAMINATION**

**Since stimulant medications have been identified as potentially hazardous to combine with *R.rosea*, subjects being recruited will be considered ineligible for the trial if they are using such medication. As part of their daily questionnaires, participants will be asked to record any medication used (prescription, over-the-counter, or natural health product) and quantity of caffeine and alcohol consumption in the past 24 hours to ensure that important co-variables can be considered in the final analysis. These questions will be administered as part of the daily MYMOP assessment.**

**From the start of the treatment, participants will be advised not to take any rhodiolaor ginseng preparations for the duration of the trial so that only the *R. rosea* treatment will influence trial outcomes. Furthermore, they will be informed that there is a 50% that they may be receiving *R.rosea*, the dose of which is being in this trial is the highest that has been supported by evidence of safety, and cautioned that they would therefore not want to “double-dose” themselves.**

- 1. **ACCOUNTABILITY OF TRIAL MEDICATION**

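### Section 6.1 allows up to four capsules (728 mg) per 24 hours, but section 6.2 allows three and caps the day at 546 mg, a figure that its own rosavin conversion does not give

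*Protocol*

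**What the plan says.** Section 6.1 (Treatment regimen) gives the daily amount in one sentence: "Subjects will be instructed to take two to four capsules of the trial medication per 24 hour period (see section 6.2".

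Section 6.2 (Dose and duration) gives the schedule. Each capsule holds 182.0 mg. The first dose is "two capsules of the trial medication at the start of their wakeful period each day". Participants then judge for themselves whether they need more within the next four hours. On the size of that second dose the section says: "The second dose willbe one capsule".

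The justification in 6.2 starts from earlier studies: "The maximum dose that has been safely used in long-term supplementation is 680 mg standardized to 3.0% rosavins for a six week period". It notes that the trial product is standardized to 2.8% rosavins and concludes: "therefore the equivalent maximum daily dose for this study is 546 mg".

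Three other statements depend on the maximum:
- Section 6.2 has daily intake self-reported: "the daily MYMOP will ask participants to record the number of capsules ingested in the past 24 hours".
- Section 6.4 promises a quantity: "They will be provided a six-week supply of their assigned study medication".
- Section 6.6 has participants told, of the active dose, that it is "the dose of which is being in this trial is the highest that has been supported by evidence of safety".

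**The concern.** The protocol gives two different maximum daily doses of its investigational product, and both stand in current text. The upper limit in 6.1 is one capsule more than the schedule in 6.2 can produce, and it exceeds the ceiling that 6.2 states.

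The conflict cannot be put down to a slip in 6.1 alone. The argument in 6.2 is a conversion for rosavin content. A weaker product needs a larger mass to deliver the same amount, so the equivalent of 680 mg should come out above 680 mg. The printed figure is below it.

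Because the extra dose is left to the participant's judgement, the written limit is the main control on daily intake. The statement to participants in 6.6 and the quantity dispensed under 6.4 both need one defined maximum. So does the analysis: section 8.2 plans to examine dose-related change as a covariate, and a day with four capsules is within the regimen under 6.1 and above it under 6.2.

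**Working it through.** **Inputs, all from the protocol**
- Capsule strength: 182.0 mg (6.2).
- Capsules per 24 hours: 2 to 4 (6.1).
- Schedule: 2 on waking, plus 1 optional (6.2).
- Stated daily maximum: 546 mg (6.2).
- Reference dose: 680 mg at 3.0% rosavins for six weeks (6.2; Table 2 lists a 42-day trial with 680 mg per day at 3.0%).
- Trial product: 2.8% rosavins (6 and 6.2).
- Treatment period: 42 days.

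**1. Reproduce the stated maximum from the schedule**

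(2 + 1) × 182 mg = 546 mg. This matches exactly, so 546 mg is the three-capsule dose.

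**2. Range under each section**
- 6.2: 2 × 182 = 364 mg to 3 × 182 = 546 mg.
- 6.1: 2 × 182 = 364 mg to 4 × 182 = 728 mg.
- Difference at the top: 728 − 546 = 182 mg, and 182 / 546 = 33%.

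**3. Try to reproduce the stated maximum from the conversion**

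Equivalent mass = reference mass × reference concentration / trial concentration.
- 680 × 3.0 / 2.8 = 728.6 mg, not 546 mg.
- With the ratio inverted by mistake: 680 × 2.8 / 3.0 = 634.7 mg, also not 546 mg.
- 546 / 728.6 = 0.749, so the printed ceiling is about 75% of what the stated reasoning gives.
- 728.6 / 4 = 182.1 mg, which is the capsule strength to within rounding. Four capsules therefore fit the conversion, and three fit the printed ceiling.

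**4. Rosavin content**

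| Dose | Calculation | Rosavins |
| --- | --- | --- |
| Cited reference | 680 × 0.030 | 20.40 mg |
| Four capsules | 728 × 0.028 | 20.38 mg |
| Three capsules | 546 × 0.028 | 15.29 mg |

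**5. Six-week supply implied by each maximum**
- Three per day: 3 × 42 = 126 capsules.
- Four per day: 4 × 42 = 168 capsules, 42 more per participant.

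The protocol does not state how many capsules each bottle holds.

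**The case against.** The best reply is that 6.1 is only a summary line. It sends the reader to 6.2, where the schedule and the ceiling agree with each other exactly, and nothing in the protocol says when or how a fourth capsule would be taken. A nurse who works from 6.2 would instruct three. What participants are told in practice comes from the information sheet and the study nurse, which this document does not show, and capsule counts are recorded daily, so over-use would be seen.

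Most of this stands. It limits the practical consequence and makes three capsules the more natural operating reading. It does not remove the conflict, because 6.1 itself says what subjects will be instructed to take, and it does not repair the derivation in 6.2, which supports the number in 6.1.

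Three stronger readings are tempting, and the documents do not support them:
- **That four capsules would be unsafe.** On the rosavin basis that 6.2 itself uses, four capsules match the cited six-week dose. They exceed the printed ceiling, but not the evidence quoted for it.
- **That participants would run out of medication.** At four per day, a fill of 126 capsules would last 126 / 4 = 31.5 days, but a fill of 126 is an assumption. A fill of 168 lasts all 42 days.
- **That the limit should apply to any rolling 24 hours, because waking times move.** Section 6.2 doses by waking day and stays within 546 mg on each. The 24-hour questionnaire item is a recall window and not a dosing rule. A rolling limit could also do harm. As an illustration with assumed times, take a participant who wakes at 15:00, takes three capsules by 19:00, and next wakes at 07:00. Under a three-capsule rolling limit nothing could be taken until 15:00, eight hours after waking, which overrides the instruction in 6.2. In a trial of shift workers that is a real trade-off and not a correction.

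**Conclusion.** The point holds as an internal inconsistency and a derivation error. Sections 6.1 and 6.2 differ by one capsule at the top of the daily range: 728 mg against 546 mg, or 182 mg (33%) above the stated ceiling. The 546 mg is the three-capsule dose and is not the rosavin equivalent of 680 mg at 3.0%, which is 728.6 mg. The text alone does not show whether the sponsor intended three capsules with a wrong explanation, or four with a wrong ceiling and second dose.

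The conclusion uses only the protocol's capsule strength, capsule counts and rosavin percentages. It does not depend on which reading was intended. No excess toxicity and no bias between arms follow from it. It should be corrected because a dose ceiling and its derivation are figures that the trial relies on.

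**What to change.** State one daily maximum, in the same words, in 6.1 and 6.2. There are two coherent versions:

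1. **Three capsules.** Change 6.1 to two to three capsules (364 to 546 mg). In 6.2, describe 546 mg as the chosen three-capsule maximum, below the rosavin equivalent of 728.6 mg, and no longer as the result of the conversion.
2. **Four capsules.** Keep the range in 6.1, correct 546 mg to 728 mg in 6.2, and make the optional second dose up to two capsules.

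In either case, fill the six-week supply to match: 126 or 168 capsules per participant. Do not add a rolling 24-hour limit.

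The first version costs only wording in two sections and leaves the schedule in 6.2 unchanged. The second also changes the optional dose, and needs 42 more capsules per participant than a three-per-day fill. Neither affects the sample size or the primary analysis.
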